#### Economic evaluation

Economic assessments are specifically tied to the study’s fourth aim. To compare the efficiency of the interventions, we will conduct a cost-effectiveness analysis (CEA) to compare arm 2 to arm 1 and arm 3 to arm 2. The difference in effects (E2-E1 or E3-E2) divided by the corresponding cost difference (C2-C1 or C3-C2) constitutes the incremental cost-effectiveness ratio (ICER) [96, 97]. E1 and C1 are treated as zero for standard well-baby care. C2 and C3 are per participant costs of each respective intervention, while E2 and E3 are mean impacts for relevant study outcomes, such as LAZ or ASQ scores. Thus, multiple ICERs are reported, one for each outcome. If the ICER for 3 vs. 2 is less than the ICER for 2 vs. 1, then the costs of the more intensive intervention are offset by improvements in outcomes and arm 3 is an efficient use of resources.

For broader generalizability, we will also aggregate all study outcomes by conducting a basic cost-benefit analysis (CBA) in which non-overlapping outcome changes for arms 2 and 3 are valued in terms of local currency. Several CBA studies on nutrition in Haiti exist [98, 99] and will provide valuation estimates for most of our study outcomes, as well as a benchmark for the efficiency of this study’s intervention relative to other child health interventions in Haiti. For the CBA, B2 and B3 are the sum of all effects (E2 and E3) for the respective study arms, valued in Haitian gourdes. Benefit-cost ratios reflect efficiency (B2/C2, B3/C3), while net differences indicate how much, if any, an arm improves net welfare [(B2-B1)-(C2-C1)] and [(B3-B2)-(C3-C2)].

For both types of economic evaluation, we will conduct sensitivity analysis of the estimates using both simple 1-way (min/max) and Monte Carlo (multi-way, probabilistic) approaches to reflect statistical confidence intervals in study impacts and costs. In the CEA, costs and effects are measured in a single year, but in the CBA, benefits include a “stream” of gains (estimated into the future) and must be discounted following standard guidelines of 3-12% [96, 97, 99], a factor also included the sensitivity analysis.

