### Study aims and hypothesized pathways

Expanding on the conceptual framework (Fig. 1) and preliminary studies across the domains of child nutrition and development, parenting, and infectious disease, the *Grandi Byen* project takes a transdisciplinary approach—spanning the biological and social sciences—to study child growth and development, while also evaluating the potential for upscaling integrated child growth and development interventions in resource-constrained settings. The project’s specific aims are to: 1) demonstrate the reproducibility of egg-based interventions in reducing childhood stunting and test its impact on development; 2) investigate the incremental benefit of *Grandi Byen* compared to egg-only and standard care groups on primary outcomes of child growth and development; 3) explore pathways of intervention impacts on child growth and development by delineating the additive and synergistic effects of biological (nutrient biomarkers, bone age, and enteric disease), psychosocial (responsive parenting, maternal mental health, cognitive stimulation), and environmental (hygiene and sanitation, diet) factors; and 4) determine whether any incremental benefits associated with *Grandi Byen* when compared to an egg only intervention and standard care are favorable relative to additional costs. Table 1 describes specific hypotheses corresponding with the study’s primary aims, aims 1 and 2.

**Table 1 Tab1:** Primary aims and study hypotheses

Primary study aims	Hypotheses
1. To demonstrate the reproducibility and feasibility of egg-based interventions in reducing childhood stunting and test its impact on development	Hypothesis 1: Linear growth will be increased by 0.30 LAZ in children receiving one egg per day compared to standard care
	Hypothesis 2: Children receiving the egg intervention will have better cognitive, motor and language development compared to standard care.
	Exploratory Question 1: Does an egg-based intervention affect social-emotional development?
2. To investigate the incremental benefit of *Grandi Byen* compared to egg only and standard care groups on primary outcomes of child growth and development.	Hypothesis 3: Children of mothers/caregivers receiving *Grandi Byen* will increase linear growth by 0.10 LAZ compared to the egg intervention.

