Disentangling which specific elements (psychosocial or hygiene and sanitation practices) of the intervention did most to enhance the nutrition intervention may be useful for future adaptations to other contexts. However, our emphasis will be on the effects of the bundled intervention, which is a common practice in medical research [58, 59]. In aim 3, we will explore hypothesized pathways from the interventions to growth and development impacts (Fig. 2). The *Grandi Byen* intervention is anticipated to influence parenting practices through improvements in caregiving and child stimulation, household environmental conditions for WASH, and child feeding for dietary diversity and ASF consumption, which may in turn reduce infectious disease incidence, improve bone maturation, and increase blood concentrations of critical nutrients. By contrast, the egg intervention alone may affect nutrition biomarkers, infection, or bone maturation to a lesser extent but is unlikely to strongly influence child development outcomes. Finally, children in the standard well-baby care group should show little or no impacts on growth and development.

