**Fig. 2 Fig2:**
[figure not shown]
Hypothesized pathways from study conditions to outcomes

The fourth aim highlights a major gap related to the effective translation and continuity of evidence-based programs in real-world settings by addressing economic considerations related to public health programming. We intentionally selected interventions (egg only and *Grandi Byen*) that are feasible for translation into programming and policy with preliminary evidence to support this [60]. Experts in implementation science recognize that there is limited research on cost-effectiveness of evidence-based interventions and emphasize that future research addresses this gap [61]. Multicomponent interventions are at risk for being expensive and complicated to reproduce in multiple contexts [62]. Moreover, costly interventions would likely not be sustainable in low-resource contexts [63]. The inclusion of an economic evaluation will allow us to determine whether any incremental benefits associated with *Grandi Byen* when compared to an egg-only intervention and standard well-baby care are favorable relative to additional costs, a question of efficiency. Given that millions of children globally living in poverty are not reaching their full developmental potential, there is a tremendous need for efficacious and cost-effective interventions to disrupt early childhood trajectories towards long-term deleterious outcomes.

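### Aim 4 sets Grandi Byen against both eggs and standard care, but the CEA lists no arm 3 vs arm 1 ratio and no dominance step

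*Protocol article*

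**What the plan says.** The fourth aim (Study aims and hypothesized pathways) asks whether the added benefits of Grandi Byen, "when compared to an egg only intervention and standard care are favorable relative to additional costs". The paragraph after Fig. 2 repeats both comparators: "when compared to an egg-only intervention and standard well-baby care are favorable relative to additional costs, a question of efficiency".

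Under Statistical analyses, Economic evaluation, the assessment is tied to this aim and the comparisons are fixed: "we will conduct a cost-effectiveness analysis (CEA) to compare arm 2 to arm 1 and arm 3 to arm 2". The ratio has effects on top: "The difference in effects (E2-E1 or E3-E2) divided by the corresponding cost difference (C2-C1 or C3-C2) constitutes the incremental cost-effectiveness ratio (ICER". For the control arm, "E1 and C1 are treated as zero for standard well-baby care". One ratio is reported per outcome. The decision rule begins "If the ICER for 3 vs. 2 is less than the ICER for 2 vs. 1"; when that holds, arm 3 is declared an efficient use of resources.

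On what to expect, the aims section says that the egg intervention alone "is unlikely to strongly influence child development outcomes". The cost-data section (Study measures, Economic evaluation) charges the purchase, storage and delivery of eggs to arms 2 and 3, and measures the costs of both arms against usual care.

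**The concern.** Two comparators are named in the aim, but the CEA gives arm 3 only one of them. The 3 vs 2 ratio answers what the parenting and WASH package adds to eggs. It does not answer what a programme with neither gets for the full cost of adopting Grandi Byen. Egg costs fall in both intervention arms, so they drop out of C3-C2, yet anyone adopting arm 3 must pay them.

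With three ordered options, the usual incremental analysis first removes options that are dominated or extendedly dominated, then computes ratios between neighbours on what remains. The plan has no such step. If arm 2 gives poor value on an outcome, it should drop out, and arm 3 should be judged against arm 1. What is at stake is the headline cost per unit gained for arm 3 on development outcomes, which the protocol intends to inform programming and policy.

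**Working it through.** **Inputs.** E1 = C1 = 0 (Economic evaluation). Table 1: egg effect on LAZ 0.30 and a further 0.10 for Grandi Byen, so E2 = 0.30 and E3 = 0.40; effect size 0.36 on cognition for Grandi Byen, used here as E3. The documents give no costs and no egg effect on cognition. Assumed: C3 = 100 units; C2 = 50, 60 or 80; E2 = 0.05 or near 0.

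**1. Where 3 vs 1 lies.** As cost per effect the ratios are C2/E2, (C3-C2)/(E3-E2) and C3/E3. The third has the summed numerators and denominators of the first two, so with positive increments it always lies between them. The same holds for the inverted ratios. Hence 3 vs 2 is more favourable than 3 vs 1, in either orientation, exactly when E2/E3 < C2/C3, that is, when eggs supply a smaller share of the effect than of the cost.

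**2. Development illustration** (E2 = 0.05, E3 = 0.36, C3 = 100; cost per SD).

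| C2 | 2 vs 1 | 3 vs 2 | 3 vs 1 | 3 vs 1 ÷ 3 vs 2 |
|---|---|---|---|---|
| 50 | 50/0.05 = 1000 | 50/0.31 = 161 | 100/0.36 = 278 | 1.7 |
| 60 | 60/0.05 = 1200 | 40/0.31 = 129 | 278 | 2.2 |
| 80 | 80/0.05 = 1600 | 20/0.31 = 65 | 278 | 4.3 |

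With E2 near 0, 3 vs 2 is about (100-C2)/0.36 = 139, 111 and 56, and the factors are 2.0, 2.5 and 5.0. As effect per cost at C2 = 50: 2 vs 1 is 0.05/50 = 0.0010, 3 vs 2 is 0.31/50 = 0.0062, and 3 vs 1 is 0.36/100 = 0.0036. The factor is again 1.7.

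**3. Growth illustration** (Table 1 LAZ effects). Eggs supply 0.30/0.40 = 75% of the effect, so 3 vs 2 flatters arm 3 only if C2 exceeds 75% of C3 (C3 < 1.333 × C2).
- C2 = 50: cost per LAZ is 167 (2 vs 1), 500 (3 vs 2) and 250 (3 vs 1). Here 3 vs 2 is the less favourable figure.
- C2 = 80: the values are 267, 200 and 250, a factor of 250/200 = 1.25.

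**4. The decision rule.**
- *Cost over effect* (lower is better). 3 vs 2 below 2 vs 1 is the definition of extended dominance of arm 2. The order is then 3 vs 2 < 3 vs 1 < 2 vs 1, so the reported arm 3 ratio is more favourable than 3 vs 1. This held in every firing case of 1,000,000 random draws with positive increments.
- *Effect over cost, as the section writes it* (higher is better). The same inequality fires when arm 3's extra spending buys less per unit cost than eggs do. 3 vs 2 is then less favourable than 3 vs 1, in every firing case of the same draws. In the development example at C2 = 50 the rule does not fire (0.0062 is not below 0.0010). In the LAZ example at C2 = 50 it does (0.10/50 = 0.002, below 0.30/50 = 0.006).
- *Either orientation.* If arm 3 costs more and does worse than arm 2, its ratio is negative, hence below a positive 2 vs 1 ratio. The rule then calls a dominated arm efficient.

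**The case against.** The strongest reply is that nothing is out of reach. With E1 = C1 = 0, the 3 vs 1 ratio is just E3 and C3 put together; arm 3 costs are measured against usual care; and the CBA reports B3/C3, in effect arm 3 against standard care if B1 is also zero (not stated). The CBA's two net differences also sum to 3 vs 1. This stands as a limit on the point: it would be too strong to infer that the CEA cannot answer the standard-care half of Aim 4. The gap is an unlisted ratio. The CBA does not fill it, because it pools all outcomes through external valuations while the CEA works outcome by outcome.

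A reader might also infer that the arm 3 ratio is too favourable whenever the efficiency rule fires. The documents do not support that. It is true for cost over effect, but the section defines effect over cost, and there the consequence reverses and the development example does not fire the rule at all.

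Nor are egg costs hidden: they enter C3 and the 2 vs 1 ratio, and a correctly labelled 3 vs 2 ratio answers a question that Aim 4 does ask. Finally, even on the cost-per-effect reading, with positive increments, the verdict for arm 3 over arm 2 is right; only the ratio to put forward changes.

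**Conclusion.** The point holds as a gap between aim and analysis: Aim 4 names two comparators, and the CEA specifies neither the arm 3 vs arm 1 ratio nor any dominance or extended-dominance check. Where eggs give a smaller share of the effect than of the cost, 3 vs 2 alone makes arm 3 look better value than it is against standard care, in either orientation. The protocol's own expectation for development points to that case, although Hypothesis 2 does foresee some egg benefit there.

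The size is about 1.7 times with eggs at half of C3, E2 = 0.05 and E3 = 0.36, and 1.7 to 5.0 over the assumed range. These figures rest on assumed costs and an assumed E2. For LAZ with the Table 1 effects there is no such inflation unless eggs exceed 75% of C3, and at 80% it is only 1.25.

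The cost-per-effect reading is the one on which the less-than rule makes sense, and there the rule marks extended dominance of arm 2. Because the section writes the ratio the other way up, the orientation must be settled before any dominance step can work. Aim 4 is not a primary aim, so this should be corrected but does not threaten the primary analyses.

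**What to change.** In Statistical analyses, Economic evaluation:

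1. Define the ICER as cost difference over effect difference, or keep effect over cost and reverse the inequality.
2. Add the arm 3 vs arm 1 ratio for each outcome (C3/E3 on the cost-per-effect form, since E1 = C1 = 0).
3. Replace the two-ratio rule: for each outcome order the arms by cost, remove any arm that is dominated or extendedly dominated, and report ratios between the remaining arms. If arm 2 drops out, 3 vs 1 is the decision ratio. The 3 vs 2 ratio can still be shown, labelled as the added value over eggs.

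The cost is a few lines of text and one more ratio per outcome, from effects and costs already planned for collection. Arm 3 may look less favourable on outcomes where eggs do little.

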#### Parenting intervention

Mothers randomized into the multicomponent *Grandi Byen* arm will simultaneously participate in the egg intervention and a psychoeducational parenting intervention conveying messages on nutrition, WASH practices, and responsive parenting. Originally developed and tested in Uganda [39], the group-based intervention was adapted and piloted in Cap-Haitien by the study team. The intervention is rooted in social learning theory and employs active and interactive learning strategies such as verbal instruction, modeling (vicarious experience), direct experience, and receiving feedback [69]. It is also based on cognitive, behavioral, and interpersonal therapeutic techniques that encourage shaping of knowledge, problem solving, practicing new behaviors and eliciting family social support [70, 71]. Messages are delivered and reinforced through a facilitated peer-group platform. The parenting intervention has 12 modules, emphasizing several key messages that emerged in our pilot work and are known to support healthy growth and development: maternal self-care, child development (stimulating play, interactive communication, and healthy families), complementary feeding with ASFs and continued breastfeeding, and household hygiene practices such as handwashing and use of soap. An adapted program manual guides each session. Table 2 details the 12 intervention modules for the *Grandi Byen* parenting program.

**Table 2 Tab2:** *Grandi Byen* parenting intervention modules

No	Title	Session summary/empirical support	Targeted mechanism
1	Parenting for strong, healthy children	Parental aspirations; challenges encountered; introduces mothers to five principles of healthy parenting covered in *Grandi Byen*: *hygiene, food, play, conversation, self-care*. **All 5 are reinforced in every session.**	Responsive parenting
2	Strong, healthy families 1	Common family stressors that can impact child development and ways to address them. Need for positive home environment to help young children to thrive; strategies to build positive mother-infant interactions.	Responsive parenting
3	Taking care of yourself	Mothers are taught to identify and link their emotions and behaviors. Positive strategies to deal with negative emotions are introduced.	

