#### Economic evaluation

*Cost data* will be obtained weekly during the parenting class for participants in arm 3 and during weekly compliance checks for participants in arms 2 and 3. For economic evaluation, research-only costs are excluded. We will measure the incremental costs of the egg (arm 2) and egg + parenting (arm 3) interventions compared to usual care (arm 1) by building participant-level cost items on time, transportation, and indirect costs into the baseline and quarterly data collection points and by measuring other intervention costs. Participants in both intervention arms may incur costs from additional time spent preparing or feeding eggs. Additionally, participants in the *Grandi Byen* arm may incur costs for time spent in the 10 sessions and for transportation. Costs to purchase, store, and deliver eggs apply to arms 2 & 3. Arm 3 also includes costs of materials, facilities for conducting the 10 sessions (community sites have an opportunity cost, even if they are provided gratis), and facilitators (for administering the intervention, 3 days of training, and transportation). Opportunity costs [88], which may differ from budgetary costs, will be measured to facilitate a social perspective.

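### The ICER is defined as effect per unit cost but judged by a lower-is-better rule, so for LAZ and ASQ the cost-effectiveness verdict on arm 3 is reversed

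*Protocol article*

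**What the plan says.** All of this is in the protocol article.

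- **Ratio** (Statistical analyses, Economic evaluation): "The difference in effects (E2-E1 or E3-E2) divided by the corresponding cost difference (C2-C1 or C3-C2) constitutes the incremental cost-effectiveness ratio (ICER". The reference arm is fixed by "E1 and C1 are treated as zero for standard well-baby care". One ratio is reported per outcome, with LAZ and ASQ scores named as examples.
- **Rule** (same section): the condition reads "If the ICER for 3 vs. 2 is less than the ICER for 2 vs. 1". When it is met, the stated conclusion for Grandi Byen is that "the costs of the more intensive intervention are offset by improvements in outcomes and arm 3 is an efficient use of resources". No clause says what follows when the condition is not met.
- **Companion analysis** (same section): the cost-benefit analysis uses benefit over cost, and a net difference of added benefit minus added cost. In both, higher is better.
- **Sign of effects** (Statistical analyses, Primary and secondary outcomes): benefit is positive for all outcomes except morbidity and infection, where it is negative.
- **Session count**: under Study measures, Economic evaluation, arm 3 participants "may incur costs for time spent in the 10 sessions and for transportation", and facility costs are also tied to 10 sessions. Under Parenting intervention: "The parenting intervention has 12 modules", and Table 2 lists 12.

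**The concern.** A lower-is-better rule belongs to a ratio of cost per unit of effect. The ratio written down is the reciprocal. No other part of the article redefines either the ratio or the rule, so an analyst who follows the text gets a verdict opposite to the intended one.

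Aim 4 asks whether the added benefit of Grandi Byen is favourable relative to its added cost, and this is the only decision rule stated for the cost-effectiveness part of that aim. As written, a costlier parenting package meets the condition more easily. The cost-effectiveness verdict could also contradict the cost-benefit result from the same data. If the conflict is left until results are known, the choice of which sentence governs could depend on the answer.

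**Working it through.** **Inputs.** E2-E1 = 0.30 LAZ (Table 1, hypothesis 1). E3-E2 = 0.10 LAZ (Table 1, hypothesis 3). E1 = C1 = 0 (Economic evaluation). The article gives no costs, so C2 = 1 is assumed as the unit and C3 is varied from 1.1 to 5. C3 > C2 follows from the listed cost items, because arm 3 carries the egg costs plus materials, facilities and facilitators. The article states no ICER value to reproduce.

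**General relation.** Let a = E2-E1, b = E3-E2, c = C2 and d = C3-C2, all positive.

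- Written rule: b/d < a/c, that is, bc < ad.
- Same rule with cost over effect: d/b < c/a, that is, ad < bc.

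Apart from exact equality, one holds only when the other fails. The written condition bc < ad is also equivalent to (a+b)/(c+d) < a/c, so arm 3 then has the lower average effect per unit cost as well.

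**Switch point for LAZ.** 0.10/(C3-C2) < 0.30/C2 if and only if C3-C2 > C2/3, that is, C3 > 1.33 × C2.

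| C3 (C2 = 1) | Effect/cost, 2 vs 1 | Effect/cost, 3 vs 2 | Rule as written | Cost/effect, 2 vs 1 | Cost/effect, 3 vs 2 | 'Less than' on cost/effect |
|---|---|---|---|---|---|---|
| 1.1 | 0.300 | 1.000 | not met | 3.33 | 1.00 | met |
| 1.2 | 0.300 | 0.500 | not met | 3.33 | 2.00 | met |
| 1.3 | 0.300 | 0.333 | not met | 3.33 | 3.00 | met |
| 1.34 | 0.300 | 0.294 | met | 3.33 | 3.40 | not met |
| 1.5 | 0.300 | 0.200 | met | 3.33 | 5.00 | not met |
| 2 | 0.300 | 0.100 | met | 3.33 | 10.0 | not met |
| 5 | 0.300 | 0.025 | met | 3.33 | 40.0 | not met |

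At C3 = 2 each added unit of cost buys one third of the LAZ that eggs buy (0.10 against 0.30), yet the text calls arm 3 efficient.

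**Arm 3 worse than eggs.** Take E3-E2 = -0.10 and C3 = 2. The written ratio is -0.10/1 = -0.10, which is below 0.30, so the rule is met. Turning the ratio over does not cure this case: 1/(-0.10) = -10, which is below 3.33. A dominance check has to come first.

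**Outcomes where benefit is negative.** For a morbidity outcome with illustrative effects E2 = -0.1 and E3 = -0.3, C2 = 1 and C3 = 2, the written ratios are -0.2 (3 vs 2) and -0.1 (2 vs 1). The rule is met, and arm 3 does buy the larger reduction per unit cost. Here the written rule points the right way unless effects are recoded.

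**The case against.** The strongest reply is that this is a slip in one sentence. The name of the ratio and the rule both fit cost per effect, so numerator and denominator were probably swapped, and a health economist would correct that at analysis without new data. The article names aims 1 and 2 as primary, and aim 4 also has a cost-benefit analysis whose net-welfare formula is correctly signed. All of this is fair, and it limits the reach of the error. It does not remove the contradiction, because the article states both sentences and they cannot both stand.

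Some stronger readings are tempting but not supported:

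- *The rule is reversed for every outcome.* It is reversed only where positive means benefit and C3 > C2. Morbidity and infection carry the opposite sign.
- *The rule rejects arm 3 when its added cost is small.* The text has no rejection clause. Below the switch point it simply does not declare arm 3 efficient.
- *The whole answer to aim 4 is reversed.* The cost-benefit net-welfare formulas are unaffected.
- *The rule is unusable without a willingness-to-pay threshold for each outcome.* Once the ratio is turned over and dominance handled, the condition is a usable one-way test relative to eggs, and the cost-benefit analysis supplies monetary values. Thresholds and acceptability curves are a debatable addition.
- *Arm 3 session costs are understated by 2/12 (17%).* That would need 12 sessions held and only 10 costed. The article says cost data are collected weekly during the parenting class, so the count of 10 need not enter the calculation, and not all arm 3 costs scale with sessions.

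**Conclusion.** The point holds within limits. The definition and the decision rule contradict each other. For LAZ and ASQ with C3 > C2, following the text labels arm 3 efficient when it buys less effect per unit cost than eggs alone, and also when it does worse than eggs. With the hypothesised 0.30 and 0.10 LAZ the switch is at C3-C2 = C2/3. That figure rests on the article's hypothesised effects; the reversal itself holds for any positive effect and cost increments. The actual costs are unknown, so the documents do not show on which side of the switch the trial will fall.

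The damage is confined to the cost-effectiveness conclusion of aim 4. The efficacy analyses and the cost-benefit net-welfare formulas stand. The difference between 10 sessions and 12 modules is a separate inconsistency of unknown size.

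**What to change.** 1. Define the ICER as (C2-C1)/(E2-E1) and (C3-C2)/(E3-E2), and keep the 'less than' rule. Alternatively, keep effect over cost and write 'greater than'. For positive increments the two give the same verdict.
2. Code every effect so that a positive value means benefit, including morbidity and infection.
3. Check dominance before forming ratios, so that E3-E2 ≤ 0 or E2-E1 ≤ 0 is not read as a low, favourable ratio.
4. State that meeting the rule shows arm 3 to be at least as efficient as eggs, and that failing to meet it does not by itself show that arm 3 is inefficient.
5. Reconcile the 10 sessions in the costing text with the 12 modules in the intervention text and Table 2, and cost the sessions actually held.

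This takes a few sentences in the analysis plan and no new data. It should be settled before any cost-effectiveness result is seen.

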Single-component interventions are known to have limited impacts on long-term growth outcomes [19]; these limitations were evident in some of our findings from follow-up and replication studies, despite the generally promising findings from the *Lulun Project*. In the *Lulun Project II* cohort study, approximately 2 years from baseline, we found evidence of growth faltering, no differences between the egg and control groups in LAZ, and significant declines in LAZ from the endline *Lulun Project* in the egg intervention group relative to the control group [20]. In Malawi, the *Mazira Project* replicated the *Lulun Project* and found that the egg intervention had limited effects on linear growth [21]. Increases in intake of proteins and multiple micronutrients were, however, observed in the egg intervention group [22]. The evidence from Malawi, in particular, demonstrates the importance of understanding contextual implications when translating evidence from one setting to another. It is implied that contextual differences between Ecuador and Malawi including dietary staples, regular consumption of other high-quality ASFs in Malawi, lower stunting prevalence in Malawi, differential infection risks, and better health-related social conditions in Ecuador may have explained the contrasting outcomes in both settings [21, 23]. Particularly, the regular consumption of fish in Malawi means that a single-component intervention with ASFs alone would have limited impacts on growth and nutrition outcomes [21]. In Haiti, however, food insecurity limits consumption of ASFs at the population level [24, 25]. Thus, an intervention incorporating ASFs may result in more positive growth outcomes in this setting. An additional contextual layer to the *Grandi Byen* study is that it recognizes urbanization as a risk factor for poor child health outcomes. Urbanization is an accelerating trend globally. Families throughout the world move to cities seeking education, healthcare, and access to markets and food systems for their children, but often face the limitations of poverty [26, 27]. This current study, distinguished from the *Lulun* and *Mazira* projects which tested the egg intervention in rural settings, may offer insight into overcoming unique urban challenges to child development.

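### The Aim 4 efficiency rule has no condition on the sign of the effects, so it labels a costlier and less effective Grandi Byen arm efficient, and inverting the ICER alone does not repair it

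*Protocol article*

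**What the plan says.** The relevant text is in the protocol article under Statistical analyses, Economic evaluation. It defines the ratio in these words: "The difference in effects (E2-E1 or E3-E2) divided by the corresponding cost difference (C2-C1 or C3-C2) constitutes the incremental cost-effectiveness ratio (ICER". It sets the reference arm by convention: "E1 and C1 are treated as zero for standard well-baby care". E2 and E3 are mean impacts on outcomes such as LAZ or ASQ scores, and a ratio is given for each outcome: "Thus, multiple ICERs are reported, one for each outcome".

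The verdict rests on a single condition, "If the ICER for 3 vs. 2 is less than the ICER for 2 vs. 1". Once this is met, the article draws its conclusion without any further requirement: "then the costs of the more intensive intervention are offset by improvements in outcomes and arm 3 is an efficient use of resources". Improvement in outcomes is asserted as the result of the inequality. It is not required as a condition for applying it.

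The same section plans one-way and Monte Carlo sensitivity analysis for both economic evaluations, to "reflect statistical confidence intervals in study impacts and costs". It also plans a cost-benefit analysis with the net difference (B3-B2)-(C3-C2). The verdict sentence refers to neither.

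**The concern.** Aim 4 asks whether any incremental benefit of Grandi Byen is favourable relative to its extra cost. Ratios can be ranked by size only when numerator and denominator are both positive. Arm 3 carries session, material, facility and facilitator costs on top of the eggs (Study measures, Economic evaluation), so C3-C2 is positive. The sign of E3-E2 is not guaranteed.

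The fraction is also the inverse of the usual ICER, while the inequality is the one that suits the usual form. The natural repair is to turn the fraction over. If that is all that is done, a dominated arm 3 still receives the favourable label, and the trial could report as efficient a programme that costs more and does less than eggs alone.

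**Working it through.** The article gives no figure for how this rule behaves, so there is none to reproduce.

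**Inputs.** 200 dyads per arm (Randomization). An egg effect of 0.30 LAZ (Hypothesis 1) is used as an illustration. Assumed, because the article does not give them: outcome SD 1, fixed costs, and r = (C3-C2)/(C2-C1) = 0.5, 1, 2 or 4. With C1 = 0, r = (C3-C2)/C2.

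**Notation.** d21 = E2-E1, d32 = E3-E2, a = C2-C1 > 0, b = C3-C2 > 0. Three forms of the rule are compared:
- as printed: d32/b < d21/a
- fraction inverted to cost/effect: b/d32 < a/d21
- effect/cost kept, inequality reversed: d32/b > d21/a

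**Step 1, dominated arm 3 (d32 < 0 < d21).** In the first two forms the left side is negative and the right side positive, so the rule always fires. In the third it can never fire. Example with d21 = 0.30, d32 = -0.10, a = b = 1:
- as printed: -0.10 < 0.30, efficient
- inverted: 1/(-0.10) = -10 < 1/0.30 = 3.33, efficient
- reversed inequality: -0.10 > 0.30 is false, not efficient

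**Step 2, how often.** The SE of d32 is sqrt(2/200) = 0.10. If arm 3 is truly worse by 0.10, P(d32 < 0) = Φ(1) = 0.841. With a true egg effect of 0.30, P(d21 > 0) = Φ(3) = 0.999. The cost/effect rule must therefore fire in about 84% of trials from this route alone. Simulation of 1,000,000 trials per setting, with arm means drawn independently, gives the following ranges over r = 0.5 to 4:

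| True effects | As printed | Inverted to cost/effect | Effect/cost, inequality reversed |
|---|---|---|---|
| Egg 0.30, arm 3 worse by 0.10 | 97-99.8% | 84-87% | 0.2-3% |
| Egg 0.30, arm 3 adds nothing | 87-99.6% | 50-63% | 0.4-13% |
| Egg 0, arm 3 adds 0.36 | 0.3-22% | 28-50% | 78-99.7% |
| No effect in any arm | 50% | 50% | 50% |

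The first and last columns are complements. The third row shows the mirror fault of the inverted form: when d32 > 0 and d21 < 0 it never fires, although arm 3 is then the more effective arm.

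**Step 3, the no-effect row.** Replacing (d21, d32) by its negative reverses each inequality, so 50% is exact for any positive costs. The dominated pattern d32 < 0 < d21 has probability 1/4 + asin(0.5)/(2π) = 1/3, because d21 and d32 correlate at -0.5.

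**Step 4, what a sign guard does.** A guard that passes arm 3 when d32 > 0 and either d21 ≤ 0 or the cost/effect inequality holds never passes an arm 3 estimated worse than eggs. Under no effect it still fires in 36-45% of trials for r = 0.5 to 4. Requiring both effects to be positive lowers that to 3-11%, but then arm 3 can never pass when the egg estimate is zero or negative.

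**Step 5, Monte Carlo on the unguarded ratio.** In a rough check (2,000 trials, r = 1, cost/effect), requiring more than 95% of draws to satisfy the rule fires in about 1% of no-effect trials. It fires in about 26% when arm 3 is truly 0.10 worse than an egg arm with effect 0.30. Adding uncertainty does not remove the sign fault.

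**The case against.** The strongest reply is that the fault depends on how the ratio is put right. If the printed effect/cost definition is kept and only the inequality is reversed, a dominated arm 3 cannot pass while the egg estimate is positive, and the rule behaves sensibly in the three scenarios with a real effect. This is correct. It limits the point to the rule as printed and to the inverted fraction. What remains under the reversed inequality is the case where both incremental estimates are negative.

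A second reply is that Aim 4 does not rest on this sentence alone. Uncertainty analysis is planned, and the cost-benefit net difference keeps its sign. A reader might infer that the economic evaluation ignores uncertainty or has no sign-safe measure; the text does not support that. The gap is that the verdict sentence is tied to neither.

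A reader might also take the 50% as a false-positive rate. It is not one. The sentence ranks point estimates and is not a stated test, and a dominance-aware ranking still fires in 36-45% of no-effect trials.

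Nor does the protocol predict a null egg effect. It says that eggs alone are something that "is unlikely to strongly influence child development outcomes", and it reports that a replication "found that the egg intervention had limited effects on linear growth". But Hypothesis 2 predicts better development with eggs, and the text argues that growth effects may be more favourable in Haiti. Finally, one ratio per outcome does not mean that a single favourable ratio settles Aim 4; the article makes no such decision.

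Dominance reporting is often left to a fuller economic plan. Here, however, the article states the verdict rule outright, and the rule as stated gives a wrong answer.

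**Conclusion.** The point holds in a limited form. As printed, and after inversion to cost/effect, the rule labels arm 3 efficient in every case where arm 3 costs more, does worse than eggs, and the egg estimate is positive. That result is algebraic and needs only positive incremental costs. The 84-87% for the inverted form, with an egg effect of 0.30 and arm 3 worse by 0.10, also rests on SD 1, fixed costs, 200 analysed per arm and the assumed cost ratios of 0.5 to 4.

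It does not follow that every correction of the ratio fails, or that Aim 4 as a whole is uninformative. The sentence should be changed because the error can favour a dominated programme and is cheap to prevent.

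**What to change.** Replace the verdict sentence in Statistical analyses, Economic evaluation, with effects coded so that positive means benefit:

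1. Classify by sign first. If E3 ≤ E2 at higher cost, report arm 3 as dominated. If E2 ≤ 0 at higher cost, report arm 2 as dominated and compare arm 3 with arm 1.
2. Compare ICERs only when both incremental effects are positive, and state the fraction and the direction of the inequality so that they agree.
3. State the efficiency conclusion as incremental net benefit, λ(E3-E2)-(C3-C2), over a stated range of λ (the value placed on one unit of effect). Take its uncertainty from the Monte Carlo work already planned. The cost-benefit net difference already has this form.

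The third step is needed because the sign guard alone leaves the verdict driven by noise when effects are small. The cost is a few lines of wording and no new data. The downside is that the result becomes an estimate with uncertainty over a range of λ and reads as less decisive than a yes or no.
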